#### VR modules

The Virtual Reality (VR) modules designed for perinatal and postpartum mothers offer a comprehensive approach to managing stress, enhancing mindfulness, and providing essential education throughout the pregnancy and postpartum journey. The NurtureVR program was created by Realized Care (previously BehaVR) and they were responsible for the development of the modules.

Nurture VR modules are divided into two main categories: Education Topics and Mindfulness Topics. The Education modules cover crucial subjects, such as the power of VR on mental health during pregnancy, coping with acute and chronic stress, the benefits of staying active, sleep and stress management, understanding C-sections, and preparing for labor. Concurrently, the Mindfulness modules complement the educational content by focusing on practices that promote relaxation, awareness, and emotional well-being, such as progressive relaxation sequences, mindfulness of breath and body, and techniques for turning off the stress response. These VR sessions also address the psychological and emotional aspects of childbirth and postpartum recovery, guiding mothers through mindfulness exercises tailored to cultivate presence, connection with their baby, and overall mental health resilience. This dual approach ensures that mothers are equipped with both the knowledge and the mental tools necessary to navigate the challenges of pregnancy, labor, and the postpartum period with greater ease and confidence. Adherence to the program will be achieved through the Administrative Control Panel (ACP), which is a back-end interface through which registered participants will be organized as well as their module start times, activity time stamps, and completion statuses. Participants will also be asked to fill out mood state surveys before and after completing each module to further ensure adherence. If participants deviate from the protocol, the study team will contact them to address concerns and to remind participants of the study requirements.

#### Recruitment plan

Prior to the recruitment of participants, flyers will be distributed through various in-person or online recruitment channels such as emails to patients’ support/advocate associations, women’s organizations, maternity and parenting forums, maternal support groups, UMiamihealthresearch.org, community outreach events, and offices at the University of Miami Miller School of Medicine Obstetrics and Gynecology department. These flyers will provide an overview of the study, including details on the structure of the intervention, time commitment, eligibility criteria, and compensation. Additionally, the flyer will feature a QR code that interested participants can scan to complete the screening form, along with contact information for the study team to address any questions potential participants may have.

Study team members will host information tables at maternal health clinics, UHealth-associated offices, and various outreach events organized for perinatal women. During these tabling sessions, research staff will introduce the study, guide participants through the study timeline, and demonstrate the use of the VR headset. Interested individuals will have the opportunity to demo the NurtureVR program and complete the screening survey, either on their personal devices or on a study-issued device provided on-site.

Expectant and postpartum Black and Latina women interested in the study will be instructed to complete a brief screening process to determine eligibility which will be facilitated through a REDCap link provided by study staff. The screening protocol (outlined in the prior section, “Participants”) ensures all participants meet the inclusion and exclusion criteria before enrollment. Participants who meet the established eligibility criteria are contacted via phone or zoom to be informed about study procedures, and asked if they would like to be enrolled and sign the consent form via REDCap to participate (See **Figure 2** for recruitment and consent process). Those deemed ineligible through the screening will be notified of their status by phone or email.

**Figure 2 f2:**
[figure not shown]
Consent process.

During recruitment, all potential participants will be informed about the compensation details. Participants who complete the 5-week intervention will receive $100 as compensation for their time and effort in participating in the research study. This information will be clearly outlined in the consent form and discussed with participants before taking part of the study.

#### Consent

After eligibility has been established, a copy of the consent form will be sent to the participant via email using REDCap for an e-signature. Interested participants will be contacted to participate in an audio or video call with a study team member. The consent document will be reviewed and explained to the participant at the time of consent, and any questions the participant might have about the study will be answered. Verbal translation will be provided for non-English speakers. Additional questions will be asked by the lab member to confirm comprehension. The participant will be asked if they consent to participate. If the participant agrees, they will be asked to sign and date the consent document electronically. Participants will receive a PDF copy of their signed consent, and a copy will be kept by UM study staff for study records and the regulatory binder.

#### Data and safety monitoring plan

Clinical site monitoring will be conducted to ensure the rights and well-being of human participants are protected, that reported trial data are complete, accurate, and verifiable, and that the conduct of the trial is compliant with the currently approved protocol/amendment(s), with Good Clinical Practices, as well as with applicable regulatory requirements including the University of Miami’s Institutional Review Board.

At the University of Miami (UM), the data manager will manage all study data under the principal investigator’s supervision. The data manager will create computerized data collection forms to ensure the integrity and accuracy of data entry. They will help to minimize the problem of missing data by resolving omissions and errors as they arise. There will be no transfer of data from UM to BehaVR. UM staff will have access to participants’ use data. Safety monitoring will include deliberate assessment and reporting of adverse events to the appropriate Institutional Review Board (IRB) and Privacy Boards. Medical monitoring will also include regular assessment of the quantity and type of serious adverse events. The Nurturing Moms Study was approved by the University of Miami IRB.

#### Statistical analysis plan

For the primary objective, General Linear Model procedures will be used to examine effects of Virtual Reality (VR) on stress over time among pregnant and postpartum moms. For the secondary objective, the User Experience Questionnaire and the Virtual Reality Neuroscience Questionnaire will be used to determine feasibility, usability, and acceptability of NurtureVR as an intervention. Measures of central tendency, and frequency distributions will be used for categorical data.

The main dependent measures will be continuous factors: maternal and pregnancy mental health and sleep scores (see **Table 1** for measures). Regression analysis will be used to explore whether sociodemographic factors (e.g., age, income, education), pregnancy factors (maternal experience scale) and postpartum factors (maternal experience scale and childbirth experience questionnaire) are associated with adverse mental and sleep health outcomes. In the statistical analysis, missing data will be handled using multiple imputation techniques to minimize bias and maintain the integrity of the analysis. Outliers will be identified through visual inspections of data distributions and statistical tests, and decisions about their inclusion will be based on their potential impact on the results and the underlying reasons for their occurrence. We will use sensitivity analyses to assess the robustness of findings. Adjustments for multiple comparisons will be made using the Bonferroni correction or false discovery rate (FDR) control to reduce the risk of Type I errors due to the number of outcomes being measured. Covariates such as age, parity (number of previous births), socioeconomic status, and baseline mental health status will be included in regression models to adjust for potential confounding factors and to provide a clearer understanding of the relationships between the intervention and outcomes. Only factors that show significant correlations in preliminary analysis will be entered in the final model. These data are significant as they will be used to generate effect size estimates (and sample sizes) for planned large-scale studies and to build preliminary exploratory models ascertaining factors that predict mental and sleep health outcomes among Black and Latina pregnant and postpartum women.

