#### Participants

Participants in the *Nurturing Moms* study will be recruited through various channels: clinical/health settings, community outreach recruitment events and community organizations, Research Match, and UMiamiHealthResearch.org. Participants will undergo a screening process in which they must meet the following inclusion criteria: 18 years old or older, speaks and understands English, Black or Latina. Additionally, they must be pregnant (less than 36 weeks) or postpartum (up to 12 months after birth). Participants will be disqualified from inclusion in the study based on the following exclusion criteria: a diagnosis of psychosis, inability to speak or understand English, or being neither pregnant (>36 weeks) nor postpartum (up to 12 months). Individuals with a history of seizures, vertigo, significant vision or hearing impairment, significant motion sickness, epilepsy, or sensitivity to flashing light/motion are also excluded from participation. Injuries to the eyes, face, neck, or arms that would make the use of the hardware uncomfortable are also grounds for exclusion. The implementation of these criteria enhances internal validity, optimizing the relevance and reliability of research findings. We aim to enroll 50 participants (25 expectant and 25 postpartum).

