#### Study settings

This is a 5-week home-based study primarily using a virtual reality headset to engage in NurtureVR. Participants can set up, customize, and navigate the program through the RealizedCare mobile or web application, which serves as the platform for their participation and is free of cost to the participants. This application is compatible with any cellular device, tablet, or desktop. Mi-Fi devices will be provided to participants who do not have reliable access to Wi-Fi. Participants will be actively encouraged to use the VR headset regularly, by completing at least one module each week (see **Table 1** for module content).

**Table 1 T1:** NurtureVR module content.

Education Topic		Mindfulness Topic
Pre-natal (Before birth)		
Week 1	Power of VR on Mental Health During Pregnancy	Progressive Relaxation sequence
Week 1	Impacts of Acute and Chronic Stress During Pregnancy Techniques to Cope	Turning off Your Stress Response
Week 2	Introduction to Mindfulness and Meditation	Mindfulness: Awareness of Breath
Week 2	Staying Active During Pregnancy	Mindfulness of Body
Week 2	Sleep and Stress During Pregnancy	Relaxing & Letting Go of Thoughts
Week 3	What is a C-Section and Why Would I need it?	Being Present I (Deattachment to Outcomes*)
Week 3	Baby’s Almost Here: Enjoying the Final Weeks of Pregnancy	Mindfulness of the Life Growing Within
Week 3	Baby’s Almost Here: Advantages of Going Full Term	Being Presence II (Deattachment of Outcomes)
Week 4	Stages of Labor	The Healing Power of Breath
Week 4	Pain Management During Labor	Letting Go of Resistance to Sensations
Week 4	Should Hypnotherapy Be in the Delivery Room?	Deepening Awareness
Week 4	What is Lamaze?	Breathing Through the Whole Body
Week 5	Handling Stress and Breastfeeding	Cultivating Connection with Your Baby I
Week 5	Breastfeeding Newborn	Cultivating Connection with Your Baby II
	Lactation Support 2	Honoring Your Body As it Is
All Weeks	Baby This Week module	
Labor (Optional)	How to Use VR During Labor to Reduce Pain	
Postpartum (anyone 6 months after giving birth)		
Week 1	10 Reasons Skin to Skin is Good for Your Baby and You	Cultivating Connection with Your Baby (Redux)
Week 1	Down-There Care: Recovery from Delivery Part 1	Healing is a Powerful Piece of the Journey
Week 2	Postpartum Nutrition	Intuitive Eating/Honoring Your Body’s Needs
Week 2	Sexual Health After Pregnancy	Mindfulness as Empowerment/Acknowledging & Making Choices About Desires

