
#### NurtureVR

The NutureVR mobile app will be installed on the participants’ mobile device. With 49 modules, the program will span five weeks prenatal, optional use during labor, and five weeks postpartum (available for anyone up to six months after childbirth). These modules are aimed to serve as a sanctuary for learning and stress relief, offering education and support for the entire family while fostering intimate connections and bonding to benefit the well-being of the mother and baby. Key features of NurtureVR include education on the effects of stress during pregnancy, 3D VR representations of fetal development, pain management simulations, mindfulness exercises for labor, and postpartum guidance covering topics such as hormonal changes, nutrition, emotional regulation, breastfeeding, and lactation training through VR-enabled practice sessions.

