The sample size was chosen with a focus on the feasibility goals of this study, while also considering its potential for generating statistically significant results. We conducted a power calculation using G*Power 3.1 to assess whether our sample size could detect meaningful changes in key outcomes. Specifically, we used a t-test to identify means: difference from a constant (one-sample case), assuming an effect size of 0.5, a power of 95%, and an alpha error probability of 0.05. This analysis yielded degrees of freedom (Df) = 44 and a required total sample size of 45. These results suggest that our planned sample size of 50 participants is sufficient to detect significant findings in this exploratory study. While the primary aim is to assess feasibility and acceptability, this sample size ensures that we have enough statistical power to observe meaningful changes in stress levels and mental health symptoms, providing valuable insights to guide future research and larger-scale trials.

The absence of a control group is another limitation that may impact the internal validity of our findings, as it makes it challenging to attribute observed changes in stress and mental health symptoms solely to the VR intervention. The decision to forgo a control group was influenced by ethical considerations, as we aim to ensure that all participants benefit from the intervention, especially given the known disparities in access to maternal mental health support among Black and Latina mothers. To address this limitation, we plan to explore the use of historical controls from similar populations in previous studies and to conduct a randomized controlled trial (RCT) in the future to better isolate the effects of NurtureVR. This future RCT would allow for more robust comparisons and a deeper understanding of the intervention’s efficacy.

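### Two cohorts of 25 are recruited and offered largely different content, but the plan names no cohort term and its power statement covers only the combined 50

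*Protocol article*

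**What the plan says.** All references are to the protocol article.

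- **Recruitment.** Participants fixes the target at 50 women, split evenly between expectant and postpartum.
- **Content.** Table 1 (Study settings) has a prenatal block and a postpartum block, each running five weeks. The NurtureVR section describes a single programme: "With 49 modules, the program will span five weeks prenatal, optional use during labor, and five weeks postpartum".
- **Primary analysis.** The Statistical analysis plan section says "General Linear Model procedures will be used to examine effects of Virtual Reality (VR) on stress over time among pregnant and postpartum moms". Its examples of covariates are age, parity, socioeconomic status and baseline mental health; cohort is not among them. It then admits to the final model only factors that correlate significantly in a preliminary analysis. The results are to supply effect sizes and sample sizes for larger trials.
- **Sample size.** The Discussion says "we used a t-test to identify means: difference from a constant (one-sample case), assuming an effect size of 0.5", with "a power of 95%, and an alpha error probability of 0.05". It reports a required total of 45 and concludes that 50 is enough to see changes in stress and mental health symptoms.
- **Control.** There is none; the Discussion lists this as a limitation.

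**The concern.** Cohort is the one factor around which recruitment is built, and there are two reasons to expect the pre-post change to differ by cohort.

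The first is content: the blocks share no education title, although some mindfulness topics recur. The second is natural course. Without a control group, whatever happens to stress over the interval is part of the measured change. For many pregnant women that interval includes childbirth. For women who enter postpartum, the birth is already past.

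If the two changes differ and only a combined change is reported, one cohort with little or no change can sit behind a clearly positive result. The averaged effect size would then pass into the sample size of a later trial, where it could be too optimistic for one cohort and too cautious for the other. The Discussion's power statement could also be taken as cover for cohort-level conclusions, which it is not.

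**Working it through.** **1. The plan's own figure.** Inputs from the Discussion: one-sample t-test, d = 0.5, power 95%, alpha 0.05. Power comes from the noncentral t distribution with n − 1 degrees of freedom and noncentrality d√n.
- One-sided alpha 0.05: n = 45, df = 44, power 0.951. This reproduces the stated 45.
- Two-sided alpha 0.05: n = 54, which does not. The stated figure therefore rests on a one-sided test that the text does not mention.

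**2. The same calculation for each cohort, d = 0.5.**

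| n | Noncentrality | One-sided power | Two-sided power |
|---|---|---|---|
| 50 (combined) | 0.5 × √50 = 3.54 | 97% | 93% |
| 25 (one cohort) | 0.5 × √25 = 2.50 | 78% | 67% |

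The change detectable with 95% power at n = 25 is 0.68 SD one-sided or 0.75 SD two-sided, against 0.47 and 0.52 SD at n = 50.

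**3. Content in Table 1.** Prenatal rows by week: 2 + 3 + 3 + 4 + 3 = 15, placing the lactation row that has no week label in week 5. Postpartum rows: 2 + 2 + 2 + 1 + 1 = 8. The ratio is 15/8 = 1.88, or 14/8 = 1.75 without the unlabelled row. Counting the all-weeks module and the optional labor module as one row each gives 17/8 = 2.1.

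**4. Which pregnant women give birth between the two surveys.** Per Timeline, headsets ship one week after baseline, use lasts five weeks, and surveys repeat three months later: 1 + 5 + 13 = 19 weeks. Assuming birth at about 40 weeks, any woman who enrols from about 40 − 19 = 21 weeks is measured before and after birth. Entry is allowed up to 36 weeks. The Abstract instead places follow-up at six weeks postpartum; on that reading every pregnant entrant's interval includes the birth.

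**5. What a combined result can hide (assumed effects, within-cohort SD of change 1, 25 per cohort).** Combined d = mean of the two changes ÷ √(1 + (half their difference)²).
- Changes 0.75 and 0.25: d = 0.50/√(1 + 0.25²) = 0.49. Two-sided power: combined 92%; cohorts alone 95% and 22%.
- Changes 1.0 and 0: d = 0.50/√(1 + 0.5²) = 0.45. Combined two-sided power 87%, although one cohort has no change.

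**6. Whether the screen would keep cohort.** Suppose the screen is a two-sided 5% test of cohort against change. For a true difference of 0.5 SD: 0.5/√(2/25) = 1.77, and Φ(1.77 − 1.96) = 0.42. Cohort would be dropped more often than kept.

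**7. Precision (SD 1).** 95% half-width per cohort: 2.064/√25 = 0.41 SD. Combined: 2.010/√50 = 0.28 SD. Difference between cohorts: about 2.01 × √(2/25) = 0.57 SD.

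**The case against.** The best defence is that the analysis sentence does not say the cohorts are pooled. It names both groups, a General Linear Model can carry a group factor, the covariate list is open-ended, and a condensed article may leave model terms to a fuller plan. The Discussion also says that the sample size was set by feasibility. All of this stands as far as it goes. What remains is that the Discussion does choose one sample and one effect size and does claim adequate power for stress and mental health changes. The screening rule, as written, gives cohort no protection.

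A reader might infer more than the article supports:

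- **A two-fold difference in exposure.** Table 1 shows content on offer. Both cohorts have five weeks and the same encouraged minimum of one module a week, which is 5 modules each, a ratio of 1.
- **Two separate interventions.** The Abstract and the NurtureVR section describe a programme that runs from pregnancy into the postpartum period, so women who enter pregnant may use both blocks. The article does not settle this.
- **A combined estimate that describes nobody.** The average over a 25/25 mix is a legitimate quantity. If the two changes are equal, it describes both cohorts.
- **A pilot meant to choose between blocks.** No stated aim says so.
- **A wrong module count.** Table 1 gives 30 + 16 + 2 = 48 if the all-weeks module counts once, but 30 + 16 + 1 + 5 = 52 if it counts weekly. The stated 49 cannot be shown wrong this way, and it does not affect the analysis.

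**Conclusion.** The concern holds in a limited form. The design builds in two cohorts with largely different content and different natural courses. The plan names no term that would separate them, applies a screen that could remove one, and states power for the combined sample only.

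At d = 0.5 the Discussion's assurance falls from 93–97% for 50 women to 67–78% for 25. The illustrations with unequal changes rest on assumed effects and a within-cohort SD of 1; they show what could be hidden, not what will happen. The childbirth argument assumes birth near 40 weeks and needs no assumption about the direction of the stress change.

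This is a gap to close before analysis. It does not invalidate the combined estimate.

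**What to change.** 1. In the Statistical analysis plan section, include cohort at entry (expectant or postpartum) and cohort-by-time in the primary General Linear Model, and exempt both from the correlation screen.
2. Report the change with its 95% interval in each cohort beside the combined figure. Do not let a non-significant interaction decide whether the cohort results are shown; the contrast is too imprecise for that (half-width about 0.57 SD).
3. Use the cohort-specific changes and intervals when sizing later trials.
4. In the Discussion, state that the calculation is one-sided and that its power applies to the combined sample only, and give the per-cohort figures (67% two-sided, 78% one-sided at d = 0.5).
5. Separately, reconcile the Abstract, Table 1 and the NurtureVR section on whether women who enter pregnant also use the postpartum block, so that exposure is defined for each cohort.

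The cost is wording only: no new data and no extra participants. The downside is wider intervals per cohort (about 0.41 against 0.28 SD), which should be stated openly.

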Unlike prior studies using VR as a reaction to treat health disturbances, the protocol described in this manuscript, *Nurturing Moms*, is designed as a *preventative* measure for Latina and African-American mothers. NurtureVR, a digital maternal mental health program, developed by BehaVR, was designed to: a) guide mothers through pregnancy via education and empathy and b) help them identify and address potential mental health concerns before these become major barriers to maternal and infant health and well-being. There is minimal research using therapeutic VR for maternal mental health in a diverse group of expecting mothers. Such work is timely, as the scientific community has only recently begun to address the importance of including diverse populations in research (25, 26). This is particularly applicable to digital health research, as the United States healthcare system continues to rapidly integrate technology into patient care. Considering this, researchers and clinicians must make a conscious effort to ensure digital health tools are accessible to all populations, especially those who have been historically neglected by the healthcare system (27).

*The Nurturing Moms* protocol (NurtureVR) addresses the aforementioned gaps in the literature by exploring Latina and Black perinatal mental health and related factors. Our primary objective is to assess whether NurtureVR reduces stress levels and mental health symptoms of pregnant and postpartum Black and Latina women. Our secondary objective is to assess whether NurtureVR improves sleep, as well as pregnancy and childbirth experiences. Our tertiary objective is to examine whether NurtureVR improves pregnancy/postpartum health literacy. We hypothesize that NurtureVR’s combination of mindfulness, relaxation, and education will be protective against postpartum depression, beneficial for pregnancy and birth experiences, and increase health literacy.

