## Methods

### Study design overview

*Nurturing Moms* is a pre-and post-design study aimed at reducing stress among expectant and postpartum Black and Latina women through a 5-week exposure to NurtureVR, a virtual reality based digital therapeutic. NurtureVR is a digital maternal mental health and educational program combining mindfulness techniques, relaxation, and virtual reality-guided imagery of pregnant and postpartum experiences. The study was designed to address pregnant women and postpartum mothers experiencing serious psychological symptoms, specifically in the Black and Latina population where mental distress rates are disproportionately higher compared to the general population. Advanced digital solutions can be leveraged to provide quality maternal mental health care that is effective and accessible to all.

The study is driven by three objectives: 1) to assess whether NurtureVR reduces stress levels and mental health symptoms of pregnant and postpartum Black and Latina women; 2) evaluate whether NurtureVR improves sleep, as well as pregnancy and childbirth experiences; and 3) investigate whether NurtureVR improve pregnancy/postpartum health literacy.

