### Data collection

#### Baseline and follow-up

After being screened and providing consent for the study, participants will receive an email with a link to complete the baseline survey online via REDCap. This survey includes questionnaires and well-validated scales that collect data on demographics, health history, stress levels, experiences of discrimination, sleep quality, emotional support, and overall pregnancy experience (see **Table 2**). Study team members may help the participant complete the baseline survey over the phone, on Zoom, or in person if necessary.

**Table 2 T2:** Study measures.

Variable*	Baseline	3 months	1 year
Tracking Form and Demographic Questionnaire	x		
Pregnancy Health History or Prenatal Screening Questionnaire (28)	x		
Perceived Stress Scale (29)	x	x	x
Everyday Discrimination Scale (Short Form) (30, 31)	x		
PROMIS^®^ Item Bank v1.0–Sleep Disturbance–Short Form 4a (32)	x	x	x
PROMIS^®^ Item Bank v2.0–Emotional Support–Short Form 4a (33)	x	x	x
Maternal Self-Efficacy Questionnaire (34)	x	x	x
Pregnancy Experience Scale (PES) (35)	x		
Childbirth Experience Questionnaire (CEQ) (36)	x		
Edinburgh Postnatal Depression Scale (EPDS) (37)	x		
User Experience Questionnaire (38)	x		
Virtual Reality Neuroscience Questionnaire (VRNQ) (39)	x		

*Some of these questionnaires have questions about the father. As the father is not relevant and is not a secondary participant in this study, these questions referring to the father have been removed.

Participants will be invited to complete the same survey three months following the completion of the intervention and will be monitored for 1 year. There will also be an optional 1-year follow-up (See **Figure 3**).

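### Pregnancy and childbirth experience are secondary-objective outcomes with no stated outcome analysis; the analysis labelled secondary addresses feasibility, and the regression names a scale not among the study instruments

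*Protocol article*

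**What the plan says.** The last paragraph of the Protocol article's Introduction states: "Our secondary objective is to assess whether NurtureVR improves sleep, as well as pregnancy and childbirth experiences". The Study design overview repeats this as the second of three objectives, to "evaluate whether NurtureVR improves sleep, as well as pregnancy and childbirth experiences".

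The Statistical analysis plan section says three things that bear on this objective.

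- On the objective by name: "For the secondary objective, the User Experience Questionnaire and the Virtual Reality Neuroscience Questionnaire will be used to determine feasibility, usability, and acceptability" of NurtureVR.
- On outcomes: "The main dependent measures will be continuous factors: maternal and pregnancy mental health and sleep scores".
- On regression, which will explore whether sociodemographic factors, "pregnancy factors (maternal experience scale) and postpartum factors (maternal experience scale and childbirth experience questionnaire) are associated with adverse mental and sleep health outcomes".

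Table 2, under Baseline and follow-up, lists 12 instruments. The PES and the CEQ are among them, each marked at baseline only. The PROMIS Sleep Disturbance form is marked at baseline, 3 months and 1 year. The text below the table says that the survey is repeated three months after the intervention, without excepting any questionnaire.

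**The concern.** An objective that asks whether the intervention improves something needs an analysis in which that something is the dependent variable. Here the plan puts pregnancy and childbirth experience on the explanatory side, as possible correlates of mental health and sleep. Such a regression shows whether women with better experiences have better mental health or sleep. It says nothing about whether NurtureVR changed the experience.

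The analysis that carries the secondary label answers a third question, how users found the product. A reader who follows the labels would report the secondary objective as addressed when two of its three components had not been analysed.

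The identity of one predictor is also open. The plan says that these exploratory models will be used to find factors that predict mental and sleep health and to inform larger studies. If the analyst picks the instrument after seeing the data, the choice is post hoc, and different instruments would give different models.

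**Working it through.** No arithmetic applies beyond counting, so the check sets the sections side by side.

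**1. Components of the objective against the stated analyses**

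| Component (Introduction; Study design overview) | Named as a dependent measure? | Role in the Statistical analysis plan | Marked in Table 2 |
|---|---|---|---|
| Sleep | Yes | Outcome | Baseline, 3 months, 1 year |
| Pregnancy experience | No | At most an explanatory factor, if the unlisted scale stands for the PES | PES: baseline only |
| Childbirth experience | No | Explanatory factor (CEQ, postpartum group) | CEQ: baseline only |

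One of three components is covered as an outcome and two are not.

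**2. The analysis labelled secondary.** It uses the User Experience Questionnaire and the Virtual Reality Neuroscience Questionnaire. As described under Study instruments, these rate the product and VR-induced symptoms. Neither measures sleep, pregnancy experience or childbirth experience.

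**3. The maternal experience scale.** The name occurs twice in the regression sentence, once for the pregnancy group and once for the postpartum group. It is not among the 12 rows of Table 2, the instruments described under Study instruments, or the four rating scales under Weekly mood state surveys. The section's pointer for measures leads to Table 1, which holds module content. Two collected instruments come near the name:

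- the PES, which rates aspects of pregnancy as uplifting or upsetting;
- the Maternal Self-Efficacy Questionnaire, which rates confidence in parenting tasks.

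The PES suits the pregnancy slot better. Neither plainly suits both slots.

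**4. What can still be fitted.** The sociodemographic factors come from the demographic questionnaire. The CEQ is collected and is named as a postpartum factor. Only the maternal experience scale terms cannot be identified.

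**5. Whether a change in experience could be estimated.** On the Table 2 marks, no: there is no follow-up PES or CEQ. On the text below the table, follow-up values would exist. The two statements conflict.

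The CEQ has a further limit. For a woman enrolled postpartum, the birth precedes NurtureVR and cannot be an outcome of it. For a woman enrolled in pregnancy, there is no value for that birth before the intervention. A CEQ score for a birth after starting NurtureVR is therefore a single measurement, not a before-and-after change.

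**The case against.** The strongest reply has four parts.

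- **Sleep is covered.** It is part of the objective, is a named dependent measure and is collected three times. This stands. A reader might infer that the whole secondary objective lacks an analysis; the document does not support that.
- **The scale name is probably a slip for the PES.** This is the likeliest reading for the pregnancy group. The same name is also used for the postpartum group, however, so the authors have to confirm what they mean. A reader might also infer that the regression cannot be run at all. That goes too far, because the sociodemographic and CEQ terms are collected and the postpartum group does not rest on the unlisted scale alone.
- **The list of dependent measures covers only the main ones, and an article may leave further outcomes to a fuller plan.** This would answer a complaint about missing detail. It does not answer a stated mismatch: the article does give an analysis for the secondary objective, and that analysis addresses something else.
- **The CEQ is listed only under postpartum factors.** This stands too. A reader might infer that multiple imputation would supply birth experiences for women who have not given birth. The document does not say so: it imputes missing data and nowhere treats a questionnaire that does not apply as missing. A short clarification is enough.

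It might also be argued that the CEQ model is weak because at most the 25 women enrolled postpartum could answer about this birth. That count depends on the Table 2 marks, which the text below the table contradicts. Correcting the wording would not enlarge the group either, so the count does not measure this defect.

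**Conclusion.** The point holds in a limited form. The objectives and the Statistical analysis plan contradict each other on what the secondary objective is. Two of its three components, pregnancy and childbirth experience, have no stated outcome analysis, and one regression predictor, named for both groups, cannot be matched to a study instrument.

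The primary stress analysis, the sleep outcome, and the sociodemographic and CEQ regression terms are not affected. In an exploratory pilot this should be corrected before analysis, but it does not undermine the study.

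The conclusion rests on the article's text and on the Table 2 marks as they appear there. If the baseline-only marks for the PES and CEQ are an error, follow-up values may exist. The mismatch between objective and analysis, and the unidentified scale, would remain.

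**What to change.** In the Statistical analysis plan section:

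1. Replace the maternal experience scale with the collected instrument intended, stated separately for the pregnancy and the postpartum group.
2. List the PES and CEQ beside sleep as dependent measures for the secondary objective, and label the two user-experience questionnaires as the feasibility analysis.
3. Reconcile Table 2 with the text below it on whether the PES and CEQ are repeated. If they are not, state that change in experience cannot be estimated.
4. Treat the CEQ as an intervention outcome only for women who gave birth after starting NurtureVR, and say whether it is summarised descriptively or compared with the historical controls mentioned in the Discussion. As an explanatory factor, use it only in women who had given birth when they completed it. State that not-applicable CEQ values are not imputed.

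Items 1, 2 and 4 cost wording only. Item 3 is also wording if the questionnaires are already in the follow-up survey. Otherwise the authors must either add them or narrow the objective. The statistical price is that CEQ results come from smaller subgroups, with wider intervals.
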